##### Use of remedial drugs

Remedial medication will be allowed when subjects’ symptoms aggravate to a health-threatening level evaluated by researchers in both groups. The decision of medication will be at the discretion of clinician for relieving abdominal symptoms and recorded in detail.

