#### Intervention description {11a}

Subjects of two groups will receive three tablets of either the *Bifidobacterium* quadruple viable tablet or the matched placebo three times a day at 30 min after breakfast, lunch, and dinner, respectively, for consecutive 4 weeks. During the treatment period, researchers will give subjects physical exams and record the results as well as vital signs. Subjects are supposed to keep completing the symptom log every day and record remedial medication and any other drug history permitted in this trial. HAMA, HAMD, IBS-QOL, and laboratory tests will be updated at the end of treatment period.

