### Relevant concomitant care permitted or prohibited during the trial {11d}

During the trial, any drugs (including antibiotics, parasympathetic inhibitors, muscle relaxants, opiates, other probiotics, antidepressants, anti-anxiety drugs, and Chinese traditional medicine) or other external therapies (including acupuncture, electro-acupuncture, and electric stimulation) that may have impact on the evaluation of the effectiveness of *Bifidobacterium* quadruple viable tablet affecting abdominal pain and diarrhea are not allowed. Drugs that have been used before baseline which are not opposite to the requirement of treatment or forbidden in the exclusion criteria will be permitted during the trial.

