### Outcomes {12}

#### Primary outcome measures

The primary outcome of this trial is the response rate. A patient is categorized as a responder if the patient is a responder in both pain intensity and stool consistency. The strength of abdominal pain will be evaluated by numerical rating scale using 0 to 10 to represent different levels of pain: 0 means no pain and 10 means severe pain (unable to perform activities of daily living). The consistency of stool will be assessed by using the Bristol Stool Form Scale (BSFS), classified into seven categories:
Type 1: Separate hard lumps, like nuts (hard to pass)Type 2: Sausage-shaped, but lumpyType 3: Like a sausage but with cracks on its surfaceType 4: Like a sausage or snake, smooth and softType 5: Soft blobs with clear cut edges (easy to pass)Type 6: Fluffy pieces with ragged edges, a mushy stoolType 7: Watery, no solid pieces, entirely liquid

The treatment will be considered effective when two criteria are reached simultaneously.

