##### Effective in improving abdominal pain for 4 weeks

It will be regarded as remission of abdominal pain for a week when the average of the highest scores of abdominal pain everyday within the week after treatment decreases by more than 30% compared with the week before the treatment. And it will be regarded as the effectiveness of drugs in improving abdominal pain when the remission of abdominal pain lasts for more than half of the treatment period (≥ 2 weeks).

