##### Effective in improving stool consistency for 4 weeks

It will be regarded as improvement of stool consistency for a week when the number of days with type 6 or 7 feces within the week after treatment decreases by more than 50% compared with the screening period. And it will be regarded as the effectiveness of drugs in improving stool consistency when the improvement of stool consistency lasts for more than half of the treatment period (≥ 2 weeks).

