## Data collection and management

### Plans for assessment and collection of outcomes {18a}

A training regarding the trial-related procedure will be conducted by the principal investigator for all staff members participating before the implementation of the trial.

In the screening period, data of following contents will be collected:
General information including demographic characteristics (gender, age) and previous and present medical history.Scores of Hamilton Anxiety and Depression Rating Scales (HAMA and HAMD) investigated by the trained raters.Physical examination (general and abdominal) and vital signs including temperature, heart rate, respiratory rate, and blood pressure.Laboratory tests including blood routine, urine routine, stool routine, and occult blood test; fasting blood glucose; tests of liver and kidney function; and electrocardiogram.Abdominal ultrasonography and colorectal colonoscopy. Urine pregnancy test only in women of childbearing age.Complete the symptom log everyday including the strength of abdominal pain, fecal traits, level of overall symptom relief, patterns of defecation, remedial medication, and any other drug history permitted in this trial.Adverse events and concomitant medication.

Patients who are admitted in the trial will be allocated randomly into two groups in a ratio of 1:1, heading to the double-blind treatment period.

In the baseline period, investigator shall give subjects physical exam again and subjects will be required to complete the IBS-QOL (quality of life) scale. Data will be recorded in CRF. Feces will be collected to study the microbiome and metabolome at this period.

In the follow-up period, subjects shall update HAMA, HAMD, and IBS-QOL again, and insist to complete the symptom log and records of concomitant drugs and adverse events every day. Researchers shall perform physical exam and record the results and vital signs as same as previous times.

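### The primary responder rule uses diary scores alone, so a patient who meets both thresholds while on a permitted remedial drug counts as a responder to the trial drug (low severity, cheap to fix)

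*Protocol article*

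**What the plan says.** **The responder rule.** Under Primary outcome measures, the protocol article states: "A patient is categorized as a responder if the patient is a responder in both pain intensity and stool consistency". It adds that meeting the two criteria is enough for treatment to be called effective.

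- Pain: the weekly mean of daily worst pain must fall by more than 30% from the week before treatment. The protocol treats this as "the effectiveness of drugs in improving abdominal pain when the remission of abdominal pain lasts for more than half of the treatment period", with at least 2 weeks given in brackets.
- Stool: days with type 6 or 7 stool must fall by more than 50% from screening. The matching phrase is "the effectiveness of drugs in improving stool consistency when the improvement of stool consistency lasts for more than half of the treatment period", again with at least 2 weeks.

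Neither criterion mentions other medication.

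**The permission.** Use of remedial drugs, listed among the secondary outcomes, allows such drugs when "symptoms aggravate to a health-threatening level evaluated by researchers in both groups". It continues: "The decision of medication will be at the discretion of clinician for relieving abdominal symptoms and recorded in detail".

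**The record.** During treatment, patients keep the daily log and "record remedial medication and any other drug history permitted in this trial" (Intervention description {11a}). The log contents listed for screening in section {18a} include "patterns of defecation, remedial medication, and any other drug history permitted in this trial".

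**The ban.** Section {11d} excludes drugs and external therapies "that may have impact on the evaluation of the effectiveness of" the trial tablet on abdominal pain and diarrhea. It does not mention the remedial drugs allowed elsewhere.

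**The concern.** A remedial drug is given to relieve abdominal symptoms, and the primary outcome measures abdominal symptoms. Under the rule as written, relief from that drug is indistinguishable from relief due to the allocated tablet, and the protocol calls the result drug effectiveness.

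The protocol recognises the problem in principle, because section {11d} bars other drugs on the ground that they may affect the efficacy assessment. It does not carry this through to the scoring of patients who receive the one class of such drugs it permits.

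At stake is the meaning of a response in a few patients. If placebo patients need remedial drugs more often, the placebo response rate rises slightly and a true difference is slightly diluted.

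**Working it through.** **Step 1. Does any section settle the status of a remedial-drug user?**

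| Section | What it settles | What it leaves open |
|---|---|---|
| Primary outcome measures and the two criteria | Response from diary scores, sufficient on their own | Any medication condition |
| Use of remedial drugs | Permission, trigger, recording | Responder status |
| Withdrawal, determined by investigator | Possible withdrawal for worsening disease needing treatment, or for forbidden drugs | Responder status; no link to remedial use |
| Withdrawal, participant request | Withdrawal recorded as treatment failure | Patients who stay in, or whom the investigator withdraws |
| Concomitant care {11d} | Ban on interfering drugs | Scoring of users of permitted drugs |
| {20b}, {20c} | Full analysis set, per protocol set, last observation carried forward | Whether a value recorded on a remedial drug may be carried forward |

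None does. A patient who worsens in week 1, is given a remedial drug, stays in, and meets both thresholds in weeks 3 and 4 is a responder.

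**Step 2. Reproduce the planning figure.** Inputs from Sample size {14}: 50% vs 30%, alpha 0.05, power 90%. Two-sided testing is from General analysis. With pooled variance and no continuity correction:

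n = [1.960·√(2·0.4·0.6) + 1.282·√(0.5·0.5 + 0.3·0.7)]² / 0.20² = (1.358 + 0.869)² / 0.04 = 124 per arm.

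This matches the protocol. The allowance also agrees: 300 − 2·124 = 52. Power is

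Φ{[d·√n − 1.960·√(2·p̄·(1 − p̄))] / √(p₁(1 − p₁) + p₂(1 − p₂))},

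which gives 90.0% at n = 124 and 94.6% at n = 150.

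**Step 3. Size of the effect.** The article gives neither a rate of remedial use nor the share c of users who become responders because of the drug. Both are assumptions. So is reading 50% and 30% as rates before any such users are added. Then p₁ = 0.50 + c·use(active) and p₂ = 0.30 + c·use(placebo).

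| Use, active / placebo | c | p₁ vs p₂ | Difference (points) | Power, 150 per arm |
|---|---|---|---|---|
| none | – | 50.0% vs 30.0% | 20.0 | 94.6% |
| 0.5% / 1% | 0.5 | 50.25% vs 30.5% | 19.75 | 94.0% |
| 1% / 2% | 0.5 | 50.5% vs 31.0% | 19.5 | 93.4% |
| 1% / 3% | 0.5 | 50.5% vs 31.5% | 19.0 | 92.1% |
| 2% / 2% | 0.5 | 51.0% vs 31.0% | 20.0 | 94.5% |
| 0.5% / 1% | 0.25 | 50.125% vs 30.25% | 19.875 | 94.3% |
| 1% / 2% | 0.25 | 50.25% vs 30.5% | 19.75 | 94.0% |
| 1% / 3% | 0.25 | 50.25% vs 30.75% | 19.5 | 93.5% |

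In patients, the 1% / 3% case with c = 0.5 means 150·0.01 = 1.5 users on active and 150·0.03 = 4.5 on placebo, so 0.75 and 2.25 added responders.

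**Step 4. The other reading of 50% and 30%.** If these already describe what the diary-only rule would yield, nothing is added to them and there is no power loss.

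**The case against.** **Handling of rescue medication belongs in the analysis plan.** Often it does, and the article refers to a statistical plan finished before database lock. But the protocol states the responder definition in full and as sufficient. A later rule would therefore change the stated endpoint rather than fill in a detail.

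**Scoring observed diary data whatever else was taken is a legitimate treatment-policy choice.** It can be, and it suits an intention-to-treat set. Remedial use is also a secondary outcome, so an imbalance between arms would be visible. However, the protocol does not present its rule as that choice. It bars other drugs because they may affect the efficacy assessment, and it already records participant-requested withdrawal as treatment failure. Scoring remedial weeks as non-response fits that approach better.

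**Hardly any patient can follow this path.** This largely stands. The patient must worsen to a health-threatening level, escape withdrawal for worsening disease, and still improve by more than 30% on pain and more than 50% on stool days in at least 2 weeks each. It limits the weight of the point, but not its correctness.

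**Stronger readings a reader might infer, which the document does not support:**

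- *A serious loss of power.* Assumed use of 5% on active and 10% on placebo with half converting would give a 17.5-point difference and 86.7% power at 150 per arm. Nothing in the article supports such rates, and they fit poorly with the trigger.
- *Power below the 90% target on 124 per arm* (86.5% in the 1% / 3% case with half converting). The full analysis set fills missing data by last observation carried forward, so 124 is not its size.
- *A false-positive risk.* Equal use leaves the difference unchanged, and heavier placebo use shrinks it. The direction would reverse only with more use on active, which the article gives no reason to expect.
- *A contradiction between the ban and the permission.* A missing cross-reference explains it.

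**Conclusion.** The point holds as a low-severity improvement. As written, relief obtained with a permitted remedial drug can be counted as response to the allocated treatment, and no section prevents this.

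The expected effect is small. In the scenarios above the difference loses at most 1.0 point and power at 150 per arm stays at 92.1% or more. Those figures rest on assumed usage and conversion rates and on taking 50% and 30% as net of remedial responders; on the other reading the loss is zero. The likely direction, slight dilution, itself assumes that placebo patients use remedial drugs more. The case for acting is therefore a clear endpoint at almost no cost, not a threat to the trial's power.

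**What to change.** Before database lock:

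1. In the primary analysis, score any week with remedial medication for abdominal pain or diarrhea, taken from the daily log, as a non-response week for both components.
2. Under last observation carried forward, do not let such a week be carried forward as a response.
3. Report the diary-only rule as a sensitivity analysis.
4. In section {11d}, name the remedial drugs as an exception to the ban.

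This adds a condition to the responder definition, a line to the missing-data rule and a cross-reference. It needs no new data or patients. Response rates would be slightly lower in both arms. The week rule is also incomplete: benefit that carries over from a remedial-drug week into later drug-free weeks still counts, so a patient treated only in week 1 could still qualify on weeks 3 and 4.

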##### Quality of life

Subjects will be asked to finish IBS-QOL scale at baseline (week 0), the end of treatment period (week 4), and follow-up period (week 6) successively.

##### Changes of microbiota and metabonomics

Stool samples of subjects will be collected at baseline (week 0) and the end of treatment period (week 4) to study whether changes of microbiota and metabonomics occur after the treatment.

##### Safety evaluation

Subjects will be instructed to report changes of their symptoms truthfully during the trial. Curative effects will be monitored, as well as adverse reactions and unexpected side effects. Adverse events must be recorded in detail whether they are related to the trial or not, including time of occurrence, clinical manifestations, severity, duration, results of laboratory tests, management and outcome, and follow-up times. History of medications is also significant to be on record to analyze causality between adverse events and experimental drugs.

##### Concern on laboratory tests

Electrocardiogram examination and laboratory tests will be performed before and after the treatment for all subjects. Routine blood, urine, stool, stool occult blood, fasting blood glucose, kidney function, and liver function tests will be included. Abnormal changes of results will be on concern and recorded within 24 h after receiving reports; researchers will be supposed to judge whether there are onsets of adverse events. Re-examinations, causality assessments, and necessary intervention will be at the discretion of clinicians.

### Participant timeline {13}

Informed consent acquirementScreening period (day − 14 to day 0 ± 3 days)Treatment period (day 1 to day 28 ± 3 days)Follow-up period (day 29 to day 42 ± 3 days)

See Fig. 1.

### Sample size {14}

Sample size calculation was performed by using PASS 13. The 4-week treatment effective rate would be adopted as the main evaluation indicator. According to the systematic review published by Zhang et al. [23], when overall symptom relief is regarded as the main evaluation indicator, the effective rate of probiotics was 50% while placebo was 30% in IBS-intervened RCTs. On this basis and combined with clinical experience, it was assumed that the 4-week treatment effective rate of the experimental group was 50% and that of the placebo group was 30%. In the case of *α* = 0.05 and the power of test was 90% (*β* = 0.10), the required sample size would be at least 124 pairs. Considering the certain shedding and withdrawal samples (52 patients), the planned sample size would be 150 cases/group, and the total would be 300 cases (into a 1:1 ratio).

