##### Participant request

Patients will be allowed requesting to quit due to their priority, and then, their treatment will abort, regarded as shedding cases and recorded as “treatment failure.” Reasons for withdrawal will be followed and recorded in symptom diary while CRF of every patients will be saved for data analysis,

When subjects with relief of symptoms are unwilling to continue taking the treatment, they need to stop the medication with the researchers’ consent. And the 4-week follow-up will still be conducted after medication as planned.

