## Statistical methods

### Statistical methods for primary and secondary outcomes {20a}

#### General analysis

Statistical analysis will be performed by using the SAS 9.4 (or updated version) software (SAS Institute Inc., Cary, NC, USA). In terms of data description, quantitative data will be presented as mean ± standard deviation, median, minimum, maximum, lower quartile (Q1), and upper quartile (Q3), respectively. The categorical data will be presented as frequency and percentage. The comparison of the two groups will be analyzed in proper methods according to the type of indicators. The quantitative data from the two groups will be compared on the basis of data distribution (variance homogeneity, normal distribution) using group *t* test or Wilcoxon’s rank-sum test. A chi-square test or Fisher’s exact test (if the chi-square test is not applicable) will be applied on the categorical data, and Wilcoxon’s rank-sum test or CMH-*χ*^2^ test for the ranked data. Two-sided tests will be applied in all statistical tests, and a *P* value equal to or less than 0.05 will be considered statistically significant (except for special instructions).

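### The 90% power is not supported for the primary analysis as planned: the response rates come from another endpoint, and the dropout allowance assumes exclusions the protocol does not make

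*Protocol article*

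**What the plan says.** All references are to the protocol article.

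- **Sample size {14}.** The rates come from a systematic review of IBS trials: "when overall symptom relief is regarded as the main evaluation indicator, the effective rate of probiotics was 50% while placebo was 30" per cent. Citing that review and clinical experience, the section continues: "it was assumed that the 4-week treatment effective rate of the experimental group was 50% and that of the placebo group was 30" per cent. With "In the case of *α* = 0.05 and the power of test was 90" per cent it arrives at 124 per group, and then: "Considering the certain shedding and withdrawal samples (52 patients), the planned sample size would be 150 cases/group".
- **Primary outcome measures.** "A patient is categorized as a responder if the patient is a responder in both pain intensity and stool consistency". Each component needs at least 2 of the 4 treatment weeks: pain down by more than 30%, and days with type 6 or 7 stool down by more than 50%.
- **Secondary outcome measures.** Overall symptom relief, rated from 1 to 7, is listed here and is not part of the primary outcome.
- **Participant request (under {11b}).** For patients who ask to leave, "their treatment will abort, regarded as shedding cases and recorded as" treatment failure, and their case report forms are kept for analysis.
- **Sections {20b} and {20c}.** The full analysis set (FAS) is built on the intention-to-treat population, and missing data are filled by last observation carried forward (LOCF).
- **General analysis.** "Two-sided tests will be applied in all statistical tests".

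**The concern.** Two inputs to the 90% do not match the analysis that the protocol describes.

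First, the planning rates were observed on a global relief rating in IBS trials. The primary outcome here is a joint pain-and-stool response in IBS-D. The section carries the rates over unchanged, does not mention that the endpoint differs, and offers no composite rate from any source.

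Second, going from 124 to 150 per arm is right only if dropouts disappear from the analysis and 124 evaluable patients remain in each arm. An FAS analysis keeps them. A patient kept as a failure pulls both response rates down and narrows the difference, which is not the same as having a smaller sample.

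At stake is how a null result would be read. It would be set against a 90% figure that was not derived for this endpoint or for this handling of dropouts. The Discussion also relies on the trial having an adequate sample size.

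**Working it through.** **Inputs.** Rates of 50% and 30%, α = 0.05, power 90%, 124 per group, 52 dropouts, 150 per group (Sample size {14}); two-sided testing (General analysis). The documents give no composite rates, so those used in step 4 are assumptions.

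**1. The plan's own figure.** Pooled two-proportion formula without continuity correction, where p̄ is the mean of the two rates:

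n = [1.960·√(2p̄(1−p̄)) + 1.2816·√(p₁(1−p₁) + p₂(1−p₂))]² / (p₁−p₂)²

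With p₁ = 0.50, p₂ = 0.30 and p̄ = 0.40: (1.960 × 0.6928 + 1.2816 × 0.6782)² / 0.04 = 124.0. Power at 124 per arm is 90.0%. The stated figure reproduces.

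**2. The dropout allowance.** 300 − 2 × 124 = 52, and 124 / (1 − 52/300) = 150. This is the calculation for dropouts who are excluded. If all 150 per arm were evaluable at 50% and 30%, power would be 94.6%.

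**3. Dropouts kept as failures.** Assume all 52 are failures, 26 per arm, and that the other 124 per arm respond at the planning rates.

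- p₁ = 0.50 × 124/150 = 0.413 and p₂ = 0.30 × 124/150 = 0.248. The difference falls from 20 to 16.5 points.
- Power = Φ{[(p₁−p₂)·√n − 1.960·√(2p̄(1−p̄))] / √(p₁(1−p₁) + p₂(1−p₂))} = Φ{(0.1653 × 12.247 − 1.960 × 0.6653) / 0.6550} = Φ(1.10) = 86.4%.
- Exact binomial enumeration gives 86.5%.
- The formula in step 1 at these rates gives 168.07, so 169 per arm would be needed for 90%.

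Power at 150 per arm by the share of each arm counted as failures: 10% gives 90.5%, 15% gives 87.8%, 17.3% gives 86.4%, 20% gives 84.7%. It falls below 90% at about 11%. The plan allows for 17.3% dropout (52/300).

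If only some of the 52 are failures and the rest respond at their arm's planning rate, which is one possible result of LOCF, power at 150 per arm is:

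| Share of the 52 counted as failures | Power |
|---|---|
| 0% | 94.6% |
| 50% | 91.1% |
| 75% | 89.0% |
| 100% | 86.4% |

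**4. The endpoint.** Same power formula, with assumed composite rates:

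| Assumed composite rates | What is held fixed | 124 completers per arm | 150 per arm, 17.3% as failures |
|---|---|---|---|
| 40% / 24% | rate ratio | 77% | 74% |
| 35% / 21% | rate ratio | 69% | 66% |
| 30% / 18% | rate ratio | 60% | 58% |
| 40% / 20% | 20-point gap | 93% | 92% |
| 35% / 15% | 20-point gap | 96% | 95% |

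Power falls when the absolute gap shrinks with the rates. It rises when a 20-point gap holds at lower rates.

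**The case against.** The calculation is correct, and the protocol labels the 50% and 30% as assumptions. Power is always conditional on its assumptions, so nothing here is an arithmetic error. That stands.

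A reader might infer that 86% is the true power of the design. The documents do not support that. The failure rule is written only for patients who ask to withdraw. Patients who stop because their symptoms have eased continue in follow-up with no failure stated. None is stated either for withdrawals by the investigator or for unblinded patients, who are marked as shedding cases. LOCF is also prescribed, and because 2 of 4 weeks suffice, a patient who improves early and then leaves might be counted as a responder. The second part of step 3 shows that the stated 90% lies inside the range of readings, with 86.4% at the low end for equal dropout in the two arms. An analysis of completers only would match the allowance and keep 90%.

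A reader might also infer that a two-part composite must respond less often than 50% and 30%, so that power must be lower. A composite rate cannot exceed the rate of either component, but overall symptom relief is not a component. Nothing in the documents ranks the composite rate against the global relief rate, and holding the rate ratio constant is only one of several possible assumptions.

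These objections limit the claim but do not remove it. The protocol bridges the endpoints only by clinical experience, and its failure and LOCF rules are not reconciled with each other or with the allowance of 52.

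**Conclusion.** The 90% is unsupported for the primary analysis as planned, though it has not been shown to be false.

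- **Dropouts.** If all 52 are failures, split equally, power at 150 per arm is 86.4%, a shortfall of 3.6 points at the protocol's own rates. This is conditional on the failure rule reaching every dropout. If dropouts are excluded, the figure is 90%.
- **Endpoint.** The direction of the error is unknown. Over the assumed composite rates examined, power at 124 completers per arm runs from 60% to 96%. That spread reflects chosen scenarios and is not an estimate of the trial's power.

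The endpoint mismatch is the larger source of uncertainty, and the dropout rule is the part that the protocol can settle from its own text.

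**What to change.** 1. State which rule, treatment failure or LOCF, governs dropouts in the FAS analysis of the primary outcome. Reconcile the Participant request text with sections {20b} and {20c}, and say how withdrawals for other reasons are classed.
2. Restate power at 150 per arm under that rule: about 86% at the current rates if all 52 are non-responders.
3. Give assumed response rates for the pain-and-stool composite, with their basis, and a short power table at 150 per arm that varies both the rates and the gap. This replaces the unconditional 90%.

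The change is a paragraph and a small table. It needs no added patients and alters no trial procedure. The cost is a stated power that is probably less favourable and openly conditional.
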